### Economic evaluation

Alongside the proposed RCT, a prospective economic study will be performed. The main question in the economic evaluation is whether the beneficial effects of preventive nebulization, compared to nebulization on indication, justifies the healthcare costs of preventive nebulization. This analysis is set up as a cost-benefit analysis (CBA), incorporating costs that will be estimated from a health system perspective over the time horizon of this study. In this economic evaluation, costs will be determined for both randomization groups during a 28-days follow-up period after ICU admission and start of mechanical ventilation. The costs of medical care will be calculated, divided into direct medical, direct nonmedical, and indirect costs, if applicable. Costs are defined as the volumes of used resources multiplied by the calculated unit prices. No discounting of costs and effects will be applied. Although, if any difference of interest in primary and/or secondary outcomes is observed, registered resource use and related costs will be compared between both intervention groups. In addition a cost-effectiveness analysis, to calculate incremental cost ratios (ICER), will be performed.

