The aim of the present trial is to determine the efficacy and safety of a strategy using preventive nebulization of acetylcysteine and salbutamol compared to a strategy using nebulization on indication in intubated and ventilated ICU patients. Furthermore, the related healthcare costs of this preventive strategy are determined. We hypothesize that a strategy using nebulization on indication in invasively ventilated ICU patients is not inferior with regard to the number of ventilator-free days and survival to day 28, but is associated with fewer side effects and lower health-related costs, compared to a strategy using preventive nebulization.

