### Primary outcome and secondary outcomes of the trial

The primary outcome of this study is the number of ventilator-free days (VFD) and survival to day 28, defined as the number of calendar days of unassisted breathing, after both ICU admission and start of mechanical ventilation to day 28, if the period of unassisted breathing lasted at least 24 consecutive hours. Unassisted breathing is defined as being extubated, ventilating with or without facemask, nasal prong oxygen, room air or tracheostomy breathing, but always without continuous positive airway pressure or pressure support of intermittent mandatory ventilation assistance. Patients who die before 28 days or are mechanically ventilated longer than 28 days are assigned zero ventilator-free days.

Secondary outcomes include clinical endpoints and cost-effectiveness outcomes. Clinical endpoints include the following: ICU and hospital length of stay (LOS); ICU, hospital, and 90-day mortality; development of moderate or severe ARDS; ventilator-associated pneumonia (VAP); development of atelectasis and pneumothorax; incidence of obstruction of the endotracheal tube (wherefore endotracheal tube exchange is indispensable); cumulative dose and duration of sedatives, cumulative dose and duration of neuromuscular blocking agents, development of delirium and incidence of side effects of nebulization of acetylcysteine and/or salbutamol. In addition, related healthcare costs will be compared from a health systems perspective over the time horizon of the trial and include direct medical and indirect costs of days of mechanical ventilation, stay in the ICU and hospital, cumulative use of sedatives and neuromuscular blocking agents, tracheostomies and ventilator-associated pneumonia.

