Compliance data are collected on a daily basis until extubation up to day 28 or death, including the quantity of secretions, type of humidifier (active or passive), amount and indication of nebulization of acetylcysteine and/or salbutamol, episodes of nebulization of other agents and side effects of nebulization of acetylcysteïne and/or salbutamol.

Resource-use parameters and unit prices are collected to estimate healthcare costs from a health systems perspective and include the medical costs of ventilation, ICU stay, in hospital stay, cumulative use of sedatives and neuromuscular blocking agents, tracheostomies and ventilator-associated pneumonia.

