## Discussion

Mechanical ventilation is associated with an impaired clearance and retention of airway secretions, which can lead to airway obstruction, atelectasis, bacterial colonization and pulmonary infection [2, 7, 54]. Preventive nebulization of mucolytic agents and bronchodilating drugs is a strategy suggested to prevent these complications [2, 4, 7]. No previous studies have addressed whether this preventive strategy is effective in a general ICU population of intubated and ventilated ICU patients.

NEBULAE is the first randomized controlled trial sufficiently powered to investigate the effectiveness, safety and costs of preventive nebulization of mucolytic agents and bronchodilating drugs compared to nebulization on indication.

All patients with an expected duration of ventilation of more than 24 hours are eligible for inclusion. Patients are excluded if they are admitted and invasively ventilated in another hospital before admission to be able to determine the total duration of ventilation and guarantee recording of all episodes of nebulization.

A concern regarding safety could be the occurrence of endotracheal tube occlusion, although nebulization of acetylcysteine is allowed in both groups in case of thick and tenacious pulmonary secretions. Furthermore, nebulization of liquids and solutions may cause obstruction and malfunction of the expiratory valve due to deposition of the aerosolized medication. To minimize this risk, awareness and training about this risk among nurses and physicians is advocated. Thereby, filters will be used and changed daily to protect the ventilator. An interim analysis on safety will be performed to evaluate these concerns. Furthermore, sedation practice could mask potential patient discomfort caused by the intervention. Similar sedation aims in both arms of the trial need to be persuaded.

The main strength of this study is the potential generalizability of its findings, considering the participation of different types of ICU’s in several hospitals as well as the broad spectrum of patients being eligible for participation. Besides the intervention under study, which is a well-known procedure familiar to nurses and physicians in all participating centers, no additional measurements or procedures are part of the study protocol. Therefore, execution of the study is straightforward and feasible.

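### The between-group cost comparison is made conditional on an outcome difference in one section and unconditional in others, and the cost-item lists do not name nebulization

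*Protocol article*

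**What the plan says.** Four places in the protocol article bear on this.

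- **Hypothesis (Background).** Nebulization on indication is expected to be non-inferior on ventilator-free days and survival to day 28. It is also expected that it "is associated with fewer side effects and lower health-related costs, compared to a strategy using preventive nebulization".
- **Outcomes (Primary outcome and secondary outcomes of the trial).** Costs are a secondary outcome: "related healthcare costs will be compared from a health systems perspective over the time horizon of the trial". No condition is attached. A list of cost items follows.
- **Data collection (Clinical data to be collected).** Resource-use parameters and unit prices are gathered and "include the medical costs of ventilation, ICU stay, in hospital stay, cumulative use of sedatives and neuromuscular blocking agents, tracheostomies and ventilator-associated pneumonia". The amount of acetylcysteine and salbutamol nebulization is recorded daily in the same section, but under compliance data.
- **Economic evaluation.** The main question is whether the benefit of preventive nebulization justifies what it costs. The section says "costs will be determined for both randomization groups during a 28-days follow-up period after ICU admission and start of mechanical ventilation", and defines cost as resource volume times unit price. It then says that "if any difference of interest in primary and/or secondary outcomes is observed, registered resource use and related costs will be compared" between the groups, and closes with "In addition a cost-effectiveness analysis, to calculate incremental cost ratios (ICER), will be performed".

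The Abstract also announces a cost-benefit and a budget-impact analysis, without any condition.

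**The concern.** There are two separate defects.

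First, the Economic evaluation makes the comparison of resource use and costs depend on what the outcomes show, and does not say how large a difference must be to count. Whether a declared secondary outcome is compared between arms would then be decided after the outcome data have been seen. The condition also points the wrong way for a non-inferiority trial with a cost hypothesis: if outcomes turn out similar, cost is what should decide between the strategies.

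Second, the lists of cost items name things that nebulization might influence downstream, but not nebulization itself. If the lists were applied as they stand, the only saving that follows directly from the design would be left out of the cost difference. The trial's declared cost question would then be answered without the cost of the strategy being tested.

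**Working it through.** The plan gives no cost figure, so there is none to reproduce. The check compares sections and makes one simple count.

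**1. Is the comparison conditional?**

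- Outcomes section: costs compared, no condition.
- Abstract: economic analyses announced, no condition.
- Economic evaluation: costs determined in both groups, no condition; resource use and costs compared between groups, conditional; incremental ratio calculated, no condition in its own sentence.

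The outcomes section and the conditional sentence give different rules for the same between-group comparison. Both cannot stand.

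**2. What would satisfy the condition?** A difference in the primary and/or any secondary outcome. Counted separately, the clinical secondary outcomes are: length of stay (2), mortality (3), ARDS, VAP, atelectasis, pneumothorax, tube obstruction (5), sedative dose and duration (2), neuromuscular blocker dose and duration (2), delirium (1) and side effects (1). The total is 2 + 3 + 5 + 2 + 2 + 1 + 1 = 16. With the primary outcome, 17 results could each open the comparison, and none has a threshold. The condition is therefore easy to meet and also discretionary.

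**3. Which items are costed?** Both lists name ventilation, ICU and hospital stay, sedatives, neuromuscular blocking agents, tracheostomies and VAP. Neither names acetylcysteine, salbutamol, nebulizers or the staff time to run them. Neither names filters, although the Discussion says "filters will be used and changed daily to protect the ventilator".

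**4. How much nebulization is involved?**

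Inputs: one session every 6 hours, each typically 20 to 30 minutes (Interventions); mean ventilation of 5 days (Sample size calculation); randomization up to 24 hours after the start of ventilation in the ICU (Patient enrollment, randomization and blinding).

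- Sessions per day: 24 / 6 = 4.
- Over 5 days: 4 × 5 = 20 sessions. Running time: 20 × 20 = 400 min to 20 × 30 = 600 min, or 6.7 to 10 hours.
- If a full day passes before randomization: 4 × 4 = 16 sessions. Running time: 320 to 480 min, or 5.3 to 8 hours.

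These are gross counts for the preventive arm. The documents do not give use in the on-indication arm. As an assumption, let that arm use a fraction f of the 20 sessions, so the between-arm difference is 20 × (1 − f):

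- f = 0: 20 sessions
- f = 0.25: 15 sessions
- f = 0.5: 10 sessions
- f = 0.75: 5 sessions

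Running time is not nursing time, and the documents give no unit price, so none of this can be turned into money here.

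**The case against.** The strongest reply is that the plan already contains what is asked for. The outcomes section promises an unconditional comparison, costs are determined in both arms regardless, and the incremental ratio carries no condition. The conditional sentence opens with a misplaced conjunction and may be loose drafting. The hypothesis is also not that all outcomes are equal: it predicts fewer side effects, and side effects are a secondary outcome, so the predicted result could itself meet the condition. Both cost lists are introduced by a form of the verb include and need not be exhaustive. With volumes recorded daily and costs defined as volume times price, nebulization could be costed without any change to the data collected. An article may leave a full price list to a fuller document.

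Most of this stands, and it limits the point. A reader might infer that the trial cannot test its cost hypothesis or will produce no cost comparison; the unconditional statements rule that out. A reader might also infer that nebulization will be counted as zero, or that the remaining cost difference would be mere noise. The lists do not exclude the item, and no prices or variances are given from which to judge the second claim.

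It is also tempting to say that the incremental ratio would change sign in about half of resamples because the effect difference is near zero. Nothing supports that figure. Resamples centre on the observed difference, which is unknown, and the sign depends on the cost difference as well. The ratio is in any case an addition to a cost-benefit analysis, and how its uncertainty is presented belongs in an analysis plan.

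What the reply does not remove is the contradiction. An unconditional promise in one section is what makes the conditional rule in another inconsistent with it. Nor does it explain why the list drawn up for costing leaves out the item on which the main economic question turns.

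**Conclusion.** The point holds in a limited form. The article gives two incompatible rules for a declared secondary outcome. One of them depends on the data, has no threshold, and fits poorly with a hypothesis of non-inferior outcome at lower cost. The cost-item lists fail to name the one resource that the strategies change by design: about 20 sessions per preventive-arm patient (16 if randomization comes a full day after ventilation starts), less whatever the on-indication arm uses.

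The session count rests on the 5-day mean from the sample size section and on full delivery of the schedule. The size of the omission in money cannot be stated from the documents. The matter is confined to the secondary economic evaluation and affects neither the primary analysis nor the sample size of 950. It is worth correcting because cost is part of the stated hypothesis.

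**What to change.** Make two changes of wording.

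1. In the Economic evaluation, delete the condition. State that resource use and costs are compared between the randomized groups in all patients, whatever the outcome results, in line with the outcomes section and the Abstract.
2. In the cost-item lists of the outcomes section and of the data-collection section, add nebulization: drugs, device, filters, and staff time. Include staff time only where the price of an ICU day does not already cover it, since otherwise it is counted twice; the article does not say which applies. Take volumes from the nebulization amounts already recorded daily in both arms, so that on-indication use is priced as well.

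The cost is an edit to the text and a few extra unit prices. No additional nebulization counts are needed from patients, and neither the sample size nor patient care changes.

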### Study organization

Trial oversight will be provided by a Trial Steering Committee composed of the principal investigators, the coordinating investigator and local investigators in the participating centers. The principal investigators and the trial coordinator are responsible for daily management of the trial. They provide assistance to the participating sites in trial management, record keeping, data management and training of the local staff. Local investigators in each site will perform randomization, supervise data collection and ensure adherence to the ICH-GCP guidelines during the trial.

### Data management

All data are coded by a patient identification number (PIN). The key is kept at the trial sites in a secure place. The data are transcribed by the local investigator into a central GCP-proof internet-based electronic CRF. Recorded data, provided with a code, will be stored securely for 15 years in archives of the Academic Medical Center, Amsterdam, The Netherlands. Data will be accessible only by the principal investigators and representatives of the Inspectorate for Healthcare of The Netherlands.

### Monitoring, safety and the reporting of adverse events

An independent GCP-certified monitor will monitor the study for data quality according to the ICH-GCP guidelines. During onsite visits, monitoring will be conducted on the following: progress of the study, rights and wellbeing of the subjects, completeness and accuracy of the recorded data, verifiability of the recorded data from source documents, compliance with the approved protocol and amendments, and compliance with GCP and applicable national regulatory requirements. Every participating center will be visited at least once every year.

Monitoring of patient safety and reviews of safety issues will be performed by a designated independent DSMB. The DSMB, consisting of three experts of critical care and mechanical ventilation and an independent statistician, watches over the ethics of the conduct of the study in accordance with the Declaration of Helsinki. The DSMB will meet by conference calls. Meetings are scheduled prior to the first patient enrolment, after inclusion of respectively 317 and 634 patients when the interim analyses for safety are performed, and after completion of patient enrolment.

As the study population consists of critically ill patients, we expect many of the patients to develop serious adverse events according to the GCP guidelines’ definition. Serious adverse events (SAEs) considered (possibly) related to the study procedure according to the local investigator will be reported to the study coordinator, SAE manager and principal investigator within 24 hours. If at least one or both (that is, the SAE manager and/or principal investigator) judges the association with the study intervention as (possibly) related, the SAE is classified as (possibly) related and reported to the reviewing Institutional Review Board and DSMB within 15 days. All (S)AEs will be provided to the reviewing Institutional Review Board and DSMB in a line listing format every 6 months. If complications occur significantly more often in the intervention group, termination of the study due to harm can be considered by the DSMB. Should the principal investigator decide not to fully implement the advice of the DSMB, the principal investigator will send the advice to the reviewing Institutional Review Board, including a note to substantiate why (part of) the advice of the DSMB will not be followed.

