### Interim analysis

Interim analyses regarding safety are performed by an independent Data Safety Monitoring Board (DSMB) when 317 and 634 patients, have been included and have completed follow-up for the primary outcome. These interim analyses are not related to the non-inferiority hypothesis.

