### General statistical considerations

Initial analyses will be performed according to the intention-to-treat (ITT) method. In addition, per-protocol (PP) analysis, including only those patients who complete the treatment according to the originally allocated protocol, will be done to check for the robustness of the results.

Continuous normally distributed variables will be expressed by their mean and standard deviation, or when not normally distributed as medians and their interquartile ranges. Categorical variables will be expressed as counts (n) and percentages (%). To analyze differences in continuous variables between the two groups, Student’s t-test will be used, or in case continuous data is not normally distributed, the Mann–Whitney U test will be used. Categorical variables will be compared with the Chi-square test or Fisher's exact tests. Statistical significance is considered to be at a *P* value <0.05 with one or two side test, depending on assessment of either non inferiority or superiority. The ICU mortality, hospital mortality, the length of ICU stay, and the length of hospital stay will be expressed with Kaplan-Meier curves.

When appropriate, statistical uncertainty will be expressed by 95 % confidence levels. All statistical analyses will be performed with the R language and environment for statistical computing [53].

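### The DSMB's written harm criterion covers one undefined group, and the side-effect outcome counts only events attributed to nebulization

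*Protocol article*

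**What the plan says.** **Acting on harm.** Under Monitoring, safety and the reporting of adverse events, the protocol article gives one criterion: "If complications occur significantly more often in the intervention group, termination of the study due to harm can be considered by the DSMB". No arm is identified. The same section sends a line listing of all adverse events to the DSMB every six months. Expedited reporting is limited to serious events judged possibly related to the study procedure.

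**Which harms are foreseen.** The Background lists bronchoconstriction from acetylcysteine, tachycardia and tachyarrhythmia from salbutamol, and disturbed ventilator triggering, all risks of giving nebulization. The Discussion adds a risk of withholding it, "A concern regarding safety could be the occurrence of endotracheal tube occlusion", next to obstruction of the expiratory valve, a risk of giving it. It says that the interim safety analysis will look at these concerns.

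**Side effects.** The secondary outcomes include "incidence of side effects of nebulization of acetylcysteine and/or salbutamol". Under Clinical data to be collected, the matching data item sits among the compliance data, as "episodes of nebulization of other agents and side effects of nebulization" of the two drugs, collected daily until extubation, day 28 or death. The aims paragraph of the Background hypothesizes fewer side effects with nebulization on indication.

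**The concern.** The two halves of the safety plan do not match the question the trial asks. Nebulization on indication is the strategy tested for non-inferiority, so harm from restricting nebulization matters as much as harm from giving it. A criterion tied to one group gives the DSMB written grounds to act on only one of these.

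The side-effect outcome raises a different problem. Critically ill ventilated patients can develop arrhythmia and bronchospasm without any nebulized drug. If such an event counts only when it is ascribed to nebulization, the preventive arm, where nebulization is scheduled every six hours, has far more opportunity to score. Part of any observed advantage for nebulization on indication would then come from the definition. Caregivers know the allocation, and attribution requires knowing the exposure, so independent outcome assessors do not remove the problem. At stake is the safety half of the trial's hypothesis; the primary endpoint is not affected.

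**Working it through.** **Part 1: the harm criterion, read both ways.**

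- If the preventive arm is meant, the criterion omits excess tube occlusion, atelectasis or pneumonia in the on-indication arm. These are the complications that preventive nebulization is meant to avert, and the Discussion itself raises tube occlusion.
- If the on-indication arm is meant, because it is the strategy tested for non-inferiority, the criterion omits bronchoconstriction, tachyarrhythmia and valve obstruction in the preventive arm.

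The article's usage does not fully settle the reading. The Abstract, the blinding text and the Discussion use 'the intervention' for nebulization, which points to the preventive arm. The Interventions section describes both arms, and the Economic evaluation compares costs "between both intervention groups". Under either reading, one set of named risks lies outside the criterion.

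**Part 2: how far the attribution-based outcome could mislead.** The article gives no figure for side effects to reproduce. The only design figure used is the sample size of 950. It is reproduced closely on the log scale: SD = √ln(1 + 0.7²) = 0.631, margin = −ln 0.9 = 0.105, one-sided 0.05 and 80% power give 445 per arm, 890 in total, and 890/0.95 = 937.

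Inputs:

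- n per arm = 950 × 0.95 / 2 ≈ 451 (Sample size calculation).
- Background event rate b: assumed 10%, with 5% and 15% as alternatives.
- Share f of the on-indication arm ever nebulized: assumed 75%, 50% or 25%.
- Drug effect: none (assumed).
- Every background event in a nebulized patient is attributed, and none in a patient never nebulized (assumed).
- Two-sided test at 0.05 (assumed for this comparison).

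The recorded rates are p₁ = b in the preventive arm and p₂ = b·f in the on-indication arm, although the true rates are equal. With d = p₁ − p₂, p̄ = (p₁ + p₂)/2, SE₀ = √[2p̄(1 − p̄)/n] and SE₁ = √[p₁(1 − p₁)/n + p₂(1 − p₂)/n], the chance of a significant false difference is about Φ[(d − 1.96·SE₀)/SE₁].

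| b | f | Recorded rates | (d − 1.96·SE₀)/SE₁ | Chance |
|---|---|---|---|---|
| 10% | 75% | 10% v 7.5% | (0.025 − 0.0369)/0.0188 = −0.63 | 26% |
| 10% | 50% | 10% v 5% | (0.050 − 0.0344)/0.0175 = 0.89 | 81% |
| 10% | 25% | 10% v 2.5% | (0.075 − 0.0316)/0.0159 = 2.73 | over 99% |
| 5% | 50% | 5% v 2.5% | 0.02 | 51% |
| 15% | 50% | 15% v 7.5% | 1.62 | 95% |

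**Opposite extreme.** Suppose only events that start during a session are attributed. Sessions last 20 to 30 minutes every six hours (Interventions), which is 80/1440 to 120/1440, or about 6% to 8% of the day. Taking 7% and f = 50%, the recorded rates become 0.7% v 0.35%. Then (0.0035 − 0.0094)/0.0048 = −1.23, a chance of about 11%. This approximation is rough, because the expected counts are only about 3 and 2 patients (451 × 0.007 and 451 × 0.0035).

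**The case against.** **Harms of withholding are measured.** A reader might infer that harm is measured in one direction only. The article does not support that. Tube obstruction, ARDS, ventilator-associated pneumonia, atelectasis, pneumothorax and mortality are secondary outcomes in both arms, none tied to nebulization. All adverse events go to the DSMB, and the Discussion places tube occlusion within the interim safety review.

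**The criterion is permissive.** It says that termination can be considered. Nothing in it bars the DSMB from advising on harm in the other arm, so a reading that the board could not act there goes too far. What remains is that the one written criterion is narrower than the concerns the article itself lists.

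**No threshold is stated.** A reader might take the word 'significantly' to mean an unadjusted 0.05 at each of the two safety looks. The article gives no level for harm. Its general rule, a "value <0.05 with one or two side test, depending on assessment of either non inferiority or superiority", does not address harm, and it says of the looks: "These interim analyses are not related to the non-inferiority hypothesis". A level may stand in a DSMB charter that is not shown. The threshold is no part of this point.

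**The on-indication arm is not free of nebulization.** Patients there may receive either drug, so side effects can be recorded in that arm. The problem concerns patients never nebulized and, to a lesser degree, the shorter exposure of those nebulized only while an indication lasts.

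**The case record form may already record these events in everyone.** The Abstract calls the side effects predefined, and daily collection is not expressly limited to nebulized patients. That is fair: non-scoring of patients never nebulized follows from how the outcome is worded and is not a stated recording rule. But the outcome as published is the attributed event, so collecting more would not by itself change what is compared.

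**The 81% is near one extreme.** This stands. It assumes full attribution, and the background rate and nebulized share are assumed too.

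**Conclusion.** The point holds in two parts.

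First, the written criterion for acting on harm names one undefined group in a comparison of two strategies with named risks on both sides. This is a defect of the stated criterion. It does not show a failure to measure harm or to report it to the DSMB. It needs no arithmetic.

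Second, the side-effect outcome is defined by attribution to nebulization and so leans towards the trial's own safety hypothesis, in an open-label setting. The direction follows from the definition. The size does not follow from the article: with a 10% background rate and no drug effect it ranges from about 11% (session-only attribution, half the on-indication arm nebulized) to over 99% (full attribution, a quarter nebulized). Under full attribution the false difference shrinks as the nebulized share rises, to 26% at three quarters. These figures illustrate how far the result depends on attribution practice and do not forecast the trial's result.

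Neither part touches the analysis of ventilator-free days.

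**What to change.** 1. In the monitoring section, replace the reference to the intervention group with 'in either group', so that the written criterion matches the concerns in the Background and Discussion.
2. List the predefined events (for example tachyarrhythmia, bronchospasm and tube occlusion) and record them in all patients of both arms on the existing daily schedule, whether or not the patient was nebulized.
3. Make the comparison of those event rates by randomized arm the side-effect analysis. Keep attribution to nebulization as a secondary description.

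The cost is protocol wording and one case record form line per event. Daily data collection is already in place, and sample size and randomization are unchanged.
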